#### 4.9.2. Archiving

All documentation forms, declarations of consent and other important trial documents are stored for at least 15 years in accordance with Section 12 (2) MPG. The patient identification list is kept separately from the trial documentation.

## **5. Ethical and regulatory aspects**

### **5.1. Independent ethics committees**

The clinical trial is only started after a favorable assessment by the responsible ethics committee has been received. In each additional trial centre, the clinical trial is only conducted after the responsible ethics committee involved has determined the suitability of the trial site and the qualification of the investigators.

### **5.2. Ethical conduct of the clinical trial**

This protocol and any subsequent amendments to the protocol have been or will be drawn up in accordance with the current version of the Declaration of Helsinki.

#### **5.2.1. Legal provisions, guidelines and standards taken into account**

The present clinical trial is conducted in accordance with the published principles of Good Clinical Practice for medical devices (EN ISO 14155-1 and -2; 2003) guideline and the applicable legal requirements (in particular the Medical Devices Act and the Ordinance on Clinical Trials of Medical Devices), due to the study design (CE-certified medical devices in indication §23b MPG) but to an adapted extent. These principles concern, among other things, ethics committee procedures, patient information and informed consent, compliance with the protocol, administrative documents, documentation of trial medication, data collection, patient records (source documents), recording and reporting of complications, preparation of inspections and audits and retention of documents. All investigators and other personnel directly involved in the trial are informed that domestic and foreign regulatory authorities, the competent federal authorities and personnel authorised by the sponsor of the clinical trial are entitled to inspect study documents and patient files at any time.

### **5.3. Notifications to authorities, authorisations and registration**

Since the present study is a study with CE-certified medical devices in the intended indication and no additional invasive measures are necessary for the study, no authorisation is required according to §23b MPG (German Medical Devices Act).

The clinical trial is also registered with a trial registry recognised by the WHO (e.g. [www.clinicaltrials.gov](http://www.clinicaltrials.gov) / DRKS).

#### **5.4. Information and consent of the test subjects**

A patient can only be included in the clinical trial if he/she has given his/her consent after having been informed verbally and in writing by an investigator about the nature, significance and scope of the clinical trial in an appropriate and comprehensible manner. At the same time as giving consent, the patient must have declared that he/she agrees to the recording of data in the course of the clinical trial and its review by persons authorised by the sponsor (e.g. monitor, auditor) and by the competent supervisory or federal authority. The patient is informed about the potential benefits and adverse effects of the investigational product and about the necessity and significance of a clinical trial. It must be clear to them that they can withdraw their consent at any time and without giving reasons, without suffering any disadvantages as a result.

The original of the written informed consent will be kept in the study folder of the trial centre. The patient will be given a copy of the written patient information including a copy of the insurance confirmation and conditions as well as the declaration of consent. In addition, a copy of both documents will be filed in the patient's file.

Patient information and declaration of consent are attached.

Patient information and consent forms as well as all other documents that participants receive are submitted to the responsible ethics committee for approval before use. As part of the monitoring process, it is checked whether the current consent form was personally dated and signed by the patient concerned before the start of the clinical trial..

#### **5.5. Clinical trials insurance**

As this is a study with CE-certified medical devices in the indication and therefore any consequential damage is covered by the product liability or public liability of the participating centres, separate clinical trials insurance is not necessary in accordance with Section 23b MPG.

Travel accident insurance is taken out for the study-related additional follow-up visits. Details of the insurance will be given in the patient information leaflet, or a copy of the insurance policy will be provided.

## **5.6. Data protection**

The provisions of the data protection laws are observed. It is ensured that all research materials and data are adequately pseudonymised in accordance with data protection regulations prior to scientific use.

The trial participants are informed about the transfer of their pseudonymised data to the recipients named therein as part of the documentation and notification obligations in accordance with point 4.74 of Good Clinical Practice for Trials with Medical Devices (EN ISO 14155-1 and -2; 2003). Persons who do not consent to the disclosure will not be included in the clinical trial.

## **6. Statistical methods and determination of the number of cases**

### **6.1. Statistical and analytical plan**

A statistical analysis plan is drawn up for the study before patient recruitment begins.

The unit of investigation in this study is the hernia, not the patient. Due to the self-controlled design of the study, both study arms are always the same size.

At least one follow-up examination is required to determine the main endpoint "recurrence". Missing follow-up examinations are replaced using LOCF (Last Observation Carried Forward), whereby this principle is also applied backwards, i.e. if a 12-month result is available but not at 6 months, the 12-month data is also used "backwards" for the 6-month results. If no single follow-up examination is available, missing values are not replaced; such cases are not included in the analysis of the "recurrence" endpoint.

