**Primary endpoint efficacy:**

All endpoints are analysed in the intention-to-treat population. In the absence of follow-up examinations, the LOCF (Last Observation Carried Forward) principle is used. Two primary endpoints are analysed (recurrence and pain); the p-value is adjusted according to Bonferroni. Pain reduction is determined separately for each side. The pain analysis is performed using the Wilcoxon signed-rank test for paired samples (alpha 0.025, two-sided). The evaluation of the recurrence rate requires a minimum observation period of 2 years. The difference in recurrence rates is expressed as a 95 % confidence interval (one-sided).

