### **4.7. Efficacy and safety parameters**

#### 4.7.1. Measurement of efficacy and safety parameters

##### *4.7.1.1. Primary and secondary outcomes*

Pain reduction is measured postoperatively and during follow-up examinations using the 0-10 point visual analogue scale (VAS). Each side of the operation is documented separately. Pain

recording is also limited to the groin area so as not to impair data quality due to other sources of pain (headache and back pain, for example). As with pain recording, the recurrence rate is also recorded separately for each side. In the event of a recurrence, the result of a clinical examination must be confirmed diagnostically (ultrasound/CT/MRI). In the absence of follow-up examinations, the LOCF principle (Last Observation Carried Forward) is applied. The recurrence rate requires at least the data from the 6-month follow-up.

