#### 6.1.5. Determination of the number of cases

First endpoint: Pain: Measurements of pain intensity using VAS are known to show high variability. Postoperative values show standard deviations (SD) of 1.5 - 2.0 points, while in follow-up examinations the mean values as well as the dispersion tend to be lower (SD 1.0 - 1.5). A larger proportion of patients will also have no pain at follow-up. In the present study, we expect this to be the case for about half of the hernias for both materials. Patients with pain mostly report intensities  $<5$  points. An expected difference of one point is therefore considered too large. A difference of 0.5 points is therefore planned here. With an SD of 1.5 points, this would mean a reduction of one third of the standard deviation. The required number of cases

to detect such a difference (paired t-test; power 90 %;  $\alpha=0.025$ ) would be 114 hernias per group, i.e. 114 patients. As a non-parametric rank test is planned for the analysis, an additional 15% is added to the number of cases, i.e. 131 hernias per group, or 131 patients.

The second endpoint "recurrence" is a non-inferiority hypothesis. A recurrence rate of approx. 5 % is expected over a period of two years (synthetic meshes). The maximum acceptable difference to the recurrence rate for the biological meshes is +3 %, i.e. a maximum recurrence rate of 8 %. If both meshes have the same recurrence rate (e.g. 5 %), then 203 cases are required to rule out a difference of more than 3 %, i.e. the 95 % confidence interval around 0 % is then [-3; +3]. If the recurrence rate for the biological meshes is 1 % higher than for the synthetic meshes, then 451 cases would be required for a 95 % confidence interval of +/- 2 %, i.e. the confidence interval around the difference of +1 % would then be [-1; +3]. This means that a difference > 3 would also be outside the confidence interval. As this is a one-sided question, a difference > 3 % can only be achieved with a  $p<0.025$ .

Thus, the second endpoint (recurrence) requires a larger number of cases ( $n=451$ ). If one also assumes a follow-up loss of approx. 10 %, this figure increases to a total of 496 people (with bilateral hernias).

The number of patients to be screened is 10% higher:  $n=546$ .

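### Recurrence has conflicting evaluability rules, and LOCF counts unobserved time as recurrence-free, which favours non-inferiority; it can also let a 1-week pain score stand for month 6

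*Protocol*

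**What the plan says.** **Missing visits.** Protocol section 6.1: "Missing follow-up examinations are replaced using LOCF (Last Observation Carried Forward), whereby this principle is also applied backwards". Its example is a missing 6-month result with a 12-month result present, where "the 12-month data is also used 'backwards' for the 6-month results". Nothing is filled in for a patient with no follow-up examination at all. The synopsis (Primary endpoint efficacy) opens with all endpoints and then says: "In the absence of follow-up examinations, the LOCF (Last Observation Carried Forward) principle is used". Section 4.7.1.1 repeats LOCF in the paragraph that covers both pain and recurrence.

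**Who is evaluable for recurrence.**
- Section 6.1: "At least one follow-up examination is required to determine the main endpoint" (recurrence).
- Section 4.7.1.1: "The recurrence rate requires at least the data from the 6-month follow-up".
- Synopsis: "The evaluation of the recurrence rate requires a minimum observation period of 2 years".

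**Visits.** Sections 4.7.1.4 and 4.9.1.5 schedule follow-up at 1 week, 6 months, 12 months and 24 months, the last with a window of 2 months either way. Recurrence and side-specific VAS are recorded at each visit.

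**Test and planning.** Section 6.1.3 sets a +3-point non-inferiority margin, judged by a 95% confidence interval (one-sided 2.5%). Section 6.1.5 assumes 5% recurrence with synthetic mesh and at most 8% with biological mesh, and raises 451 patients to 496 for about 10% loss. On pain, it gives SDs of 1.5-2.0 for postoperative values, "while in follow-up examinations the mean values as well as the dispersion tend to be lower" (SD 1.0-1.5).

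**The concern.** The first two evaluability rules give different analysis sets for a primary endpoint. A patient seen only at 1 week is in under section 6.1 and out under section 4.7.1.1.

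The larger issue is what LOCF does to recurrence. Carrying an observed recurrence forward is sound. Carrying its absence forward treats the unobserved remainder of the 2 years as recurrence-free. A patient lost to follow-up normally takes both groins along, so the imputation mostly adds pairs with no event on either side. Both rates shrink by the same factor, and so does their difference. Against a fixed absolute margin, that bias favours the hypothesis the trial hopes to confirm. Adopting section 4.7.1.1 does not remove it, because a recurrence-free 6- or 12-month visit would still be carried to 24 months.

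For pain, the only scheduled follow-up before 6 months is at 1 week. If no later value exists, early postoperative pain fills a 6-month cell.

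**Working it through.** **Inputs from the Protocol.** Margin +3 points and one-sided 2.5% (6.1.3); rates 5% and 8%, loss about 10%, N = 496 (6.1.5).

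**Assumed, shown as ranges.** f, the share of lost patients' 2-year recurrences already recorded before loss: 0 to 0.5. φ, the within-patient correlation of recurrence between sides: 0 to 0.3. A loss of 20%, to show the trend.

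**Step 1: the plan's own figures.** The confidence-interval formula n = 1.96² p(1−p)/h² with p = 0.05 gives:
- h = 0.03: 202.8, rounded up to 203 (stated 203);
- h = 0.02: 456.2, rounded up to 457 (stated 451, 1.3% apart).

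Then 451 × 1.1 = 496.1, matching the stated 496. The inputs are therefore read as the plan uses them.

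**Step 2: effect of LOCF on the rates.** With loss L, both rates are multiplied by k = (1 − L) + L·f. At L = 0.10:

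| f | k | synthetic | biological | difference |
|---|---|---|---|---|
| no loss | 1.000 | 5.00% | 8.00% | 3.00 points |
| 0.50 | 0.950 | 4.75% | 7.60% | 2.85 points |
| 0.25 | 0.925 | 4.63% | 7.40% | 2.78 points |
| 0 | 0.900 | 4.50% | 7.20% | 2.70 points |

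**Step 3: type I error at the margin.** With a and b the shrunken rates:

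SE = √{[a(1−a) + b(1−b) − 2φ√(a(1−a)b(1−b))]/496}

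Type I = Φ((0.03 − 0.03k)/SE − 1.96)

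Example, L = 0.10, f = 0, φ = 0: SE = √[(0.045·0.955 + 0.072·0.928)/496] = 0.0149. The shift is 0.003/0.0149 = 0.20, and Φ(−1.76) = 3.9%.

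| L | f | φ = 0 | φ = 0.3 |
|---|---|---|---|
| 10% | 0.50 | 3.1% | 3.3% |
| 10% | 0.25 | 3.5% | 3.7% |
| 10% | 0 | 3.9% | 4.3% |
| 20% | 0.25 | 5.0% | 5.6% |
| 20% | 0 | 6.3% | 7.3% |

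**Step 4: simulation check.** Paired multinomial draws with independent sides and 200,000 runs gave 2.7% with complete data (N = 496) and 2.8% with observed cases only (N = 446). With LOCF they gave 3.4% (L = 10%, f = 0.5) and 4.2% (L = 10%, f = 0). The formula and the simulation agree on direction and size.

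**Step 5: pain.** If a share m of patients has a 1-week value carried, the analysed mean difference is (1 − m)·D6 + m·D1, where D6 and D1 are the between-side differences at 6 months and 1 week. The Protocol gives neither m nor D1, so the bias cannot be sized. The formula also describes a mean, whereas the planned test is a rank test.

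**The case against.** **Inflation is about one point at the planned loss.** The 4.3% figure needs every lost patient to leave before any recurrence is seen, in effect after the 1-week visit, and section 4.7.1.1 would bar those patients. If patients are last seen at 6 or 12 months and the hazard is roughly even (an assumption), f is 0.25-0.5 and the error is 3.1-3.7%. This stands and limits the severity. The figures of 5% and above need twice the planned loss.

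**Three contradictory rules?** A reader might count the synopsis as a third incompatible rule, and even conclude that an in-window month-22 visit fails it. The same synopsis paragraph prescribes LOCF for absent visits, so its 2-year requirement can be read as the endpoint horizon, and the visit schedule accepts the window. The clear conflict is between sections 6.1 and 4.7.1.1; the synopsis needs clarifying.

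**Discharge pain carried to 6 months?** Not supported. Section 6.1 replaces missing follow-up examinations, and the flow chart lists discharge separately from follow-up.

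**Two answers for one missing 6-month value?** Where a 12-month value exists, the example in section 6.1 most naturally means that it is used. Its precedence over a 1-week value is not stated outright, but the 1-week carry arises mainly when later visits are missing too. A 12-month score is not acute pain, so deleting the backward rule would be a preference.

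**Is the pain result biased in a known direction?** A reader might infer this from the higher early values. In a within-patient comparison a shared level cancels; only a between-side difference at 1 week would bias the result, and none is given.

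**Is this for the SAP?** Details of imputation and sensitivity analyses can be left to it. The LOCF rule and the evaluability conditions are fixed in the Protocol itself, so this objection does not remove the point.

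**Conclusion.** The point holds in a limited form. Sections 6.1 and 4.7.1.1 disagree on who enters the recurrence analysis, and the synopsis wording should be clarified or reconciled with them. LOCF for recurrence is anti-conservative for non-inferiority under either section. With true rates at the margin, 496 patients and 10% loss, the expected difference drops from 3.0 to 2.70-2.85 points and one-sided type I error goes from 2.5% to about 3.1-4.3%. This rests on the assumed ranges for f and φ and on both sides of a patient being lost together. It is modest and grows with loss.

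For pain, the stated rule permits a 1-week score to serve as the 6-month value when nothing later exists, although section 6.1.5 itself treats early and later values as different in mean and spread. Whether this biases the comparison, and which way, cannot be determined from the documents. Severity: should-fix.

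**What to change.** **Recurrence.**
- State one evaluability rule in sections 6.1 and 4.7.1.1 and the synopsis, accepting the 24-month visit within its 2-month window.
- Carry forward only an observed recurrence. Otherwise censor the side at its last examination.
- Estimate the 24-month risk difference from side-specific Kaplan-Meier curves, with a confidence interval that respects the within-patient pairing (for example, a bootstrap that resamples patients). Give complete pairs as a sensitivity analysis.

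**Pain.**
- Do not carry 1-week values to 6 months.
- If the backward rule is kept, state that the 12-month value takes precedence.
- Analyse observed 6-month pairs as the primary or a sensitivity analysis, and say which.

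**Cost.** Wording changes and modest programming. Kaplan-Meier curves and side-specific follow-up are already planned, so no new data are needed. The downside is slightly fewer pain pairs and a slightly wider recurrence interval. Observed-pair and censored analyses also rest on an assumption of their own, that loss is ignorable, which should be stated.

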#### **6.1.1. Study populations**

The study is evaluated according to the intention-to-treat (ITT) principle, i.e. the right or left hernia is allocated to the group with biological mesh or synthetic mesh according to randomisation.

If mix-ups occur during the course of the study, i.e. the wrong sides were operated on (i.e. right/left instead of left/right), or both sides were operated on using the same procedure, then a protocol violation has occurred. In this case, a "Per-Protocol" (PP) analysis and an "As Treated" analysis are also carried out. In the per-protocol analysis, patients with protocol violations are excluded; in the as-treated analysis, the respective hernia is assigned to the material group (biological or synthetic).

Surgery-specific complications are also reported according to "As-Treated".

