#### **4.6. Treatments**

##### **4.6.1. Treatments used**

Patients with bilateral inguinal hernias will undergo an operation that corresponds to routine laparoscopic hernia surgery (TAPP or TEP) and is performed according to the guidelines of the IEHS (International Endohernia Society) after consenting to participate in the study. The only deviation is that one side is specifically treated with one side is supplied with a synthetic mesh material and the other with biological mesh material. Randomisation is used to decide which side is supplied with the biological mesh material. The other side is then supplied with the synthetic counterpart. Both sides must be treated using the same technique (TAPP or TEP). The implant remains permanently in the body or, in the case of the biological mesh material, is replaced by the body's own tissue; follow-up treatment is not normally necessary.

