### Surgery (D1)

The operation must be standardised in accordance with the "Guidelines for laparoscopic (TAPP) and endoscopic (TEP) treatment of inguinal hernia" published by the International Endohernia Society (IEHS). This is ensured by the fact that only hernia centres participate in the study.

Both sides must be treated with the same surgical procedure (TEP or TAPP), the only difference being the mesh used (biomesh or synthetic mesh).

Complications are recorded for the first time (see also 2.3 and 4.9.1.3)

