#### 6.1.3. Primary outcomes

In this study, two primary endpoints are considered in parallel: pain intensity and recurrence. The total error of the first type ( $\alpha=0.05$ ) is distributed equally between the two endpoints according to a Bonferroni adjustment ( $\alpha=0.025$  in each case).

Pain intensity is recorded at 6 months after the operation using a visual analogue scale (VAS; 0-10 points) and tested for difference. Two pain values are recorded for each patient, separately for the left and right groin area. This means that dependent data is available. As experience shows that pain values are not symmetrically distributed, the evaluation is carried out non-parametrically with a rank test (Wilcoxon's rank sum test). The p-value is 0.025.

The second primary endpoint is the recurrence rate. The occurrence of a recurrence is recorded at several follow-up examinations over a period of 2 years after the procedure. A recurrence must be confirmed diagnostically. This endpoint will be tested for non-inferiority. It is expected that the recurrence rate with a biological mesh will be lower, the same or at most 3 % higher than the recurrence rate with a synthetic mesh. A range of  $\pm 3$  % is thus defined as still comparable. A 95 % confidence interval is determined for the observed difference in recurrence rates (biological - synthetic). If the value of  $+3$  % is not within this confidence interval, the biological mesh is considered non-inferior. Non-inferiority is a one-sided question. The 95 % confidence interval here corresponds to a one-sided question with a p-value of 2.5 %, as required by the Bonferroni correction.

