#### 6.1.4. Secondary outcomes

The secondary outcomes are presented descriptively and compared exploratively. The recurrences are visualised using Kaplan-Meier curves.

Complications are compared in the as-treated collectives.

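### Section 6.1.1 words a protocol violation so that it contradicts the surgical rules, and recurrence non-inferiority is decided on the ITT set alone, where mesh mix-ups favour the claim

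*Protocol*

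**What the plan says.** Section 6.1.1 follows the ITT principle: "the right or left hernia is allocated to the group with biological mesh or synthetic mesh according to randomisation". It then deals with mix-ups. If the sides were exchanged, or if "both sides were operated on using the same procedure, then a protocol violation has occurred", a PP analysis (violators excluded) and an as-treated analysis (each hernia counted under the material it received) are added.

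Two other places govern how the two sides are operated on. The Surgery (D1) text in Section 4.7.1.4 states: "Both sides must be treated with the same surgical procedure (TEP or TAPP". Section 4.6.1 states: "Both sides must be treated using the same technique (TAPP or TEP".

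On the decision, the Synopsis states: "All endpoints are analysed in the intention-to-treat population". Section 6.1.3 says of recurrence: "This endpoint will be tested for non-inferiority". It concludes non-inferiority when +3% lies outside the 95% confidence interval for the difference (biological minus synthetic), at a one-sided level of 2.5%. It names no analysis set and gives the PP result no part in the conclusion.

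**The concern.** There are two linked problems.

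The first is wording. The sentence that determines who leaves the PP set uses the word that the surgical sections use for something both sides must share. Taken literally, it would remove the patients who were operated on as required.

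The second is the decision rule. One population principle serves two hypotheses that need opposite protection. For pain, a test for difference, wrong-mesh treatment under ITT weakens a true effect and so works against a positive finding. For recurrence, the same weakening moves a harmful difference towards zero and helps the non-inferiority claim. The analysis that would guard against this, PP, is planned only as an addition, and nothing says what happens if it disagrees with ITT. At stake is the error rate of one of the two primary conclusions.

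**Working it through.** **Wording.** Section 6.1.1 treats the same procedure on both sides as a violation. The Surgery (D1) text demands the same surgical procedure on both sides, and Section 4.6.1 demands the same technique. The direct clash is with Surgery (D1), which uses the same noun. Within Section 6.1.1, the sentence is introduced as a case of mix-ups, and the as-treated rule that follows regroups hernias by material. So the intended meaning is the same mesh material on both sides.

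**Which mix-ups dilute the ITT difference.** Let D be the true difference in recurrence (biological minus synthetic), and assume that mix-ups are unrelated to outcome.

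- Swapped sides in a share s of patients: these patients contribute -D, so the ITT difference is (1-s)D - sD = D(1-2s).
- Biological mesh on both sides in a share m: these patients contribute 0, so the ITT difference is D(1-m).
- Synthetic mesh on both sides: Section 4.4 excludes a participant in whom no biomesh treatment is performed, so these patients do not dilute the result.

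**Inputs from Sections 6.1.3 and 6.1.5.** Synthetic rate 5%, margin +3 points (8% for biological mesh), 451 analysable patients, one-sided level 2.5%.

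**The plan's own figures.** n = 1.96² × 0.05 × 0.95 / w² gives 202.7 for w = 0.03 (stated 203) and 456.2 for w = 0.02 (stated 451, about 1% lower). The plan's half-width of 2 points implies a standard error (SE) of 2/1.96 = 1.02 points. That formula uses the variance of a single proportion. With 8% against 5% and independent sides, SE = √[(0.08 × 0.92 + 0.05 × 0.95)/451] = √(0.1211/451) = 1.64 points. Both are carried as a range.

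**False non-inferiority rate at D = +3.** Rate = Φ(-1.96 + (3 - d)/SE), where d is the ITT difference in points. For 5% swapped, d = 3(1 - 0.10) = 2.70. With SE 1.02 this is Φ(-1.96 + 0.294) = Φ(-1.666) = 4.8%. With SE 1.64 it is Φ(-1.96 + 0.183) = Φ(-1.777) = 3.8%.

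| Mix-up (assumed share of 451) | ITT difference | Rate, SE 1.64 | Rate, SE 1.02 |
|---|---|---|---|
| None | 3.00 | 2.5% | 2.5% |
| Swapped 1% (about 5 patients) | 2.94 | 2.7% | 2.9% |
| Swapped 2% (about 9) | 2.88 | 3.0% | 3.3% |
| Swapped 5% (about 23) | 2.70 | 3.8% | 4.8% |
| Biological both sides 5% (about 23) | 2.85 | 3.1% | 3.5% |
| Biological both sides 10% (about 45) | 2.70 | 3.8% | 4.8% |

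**PP set.** Removing the mix-ups returns d to 3.00 and the rate to 2.5%, if they are unrelated to outcome. About 442 patients remain at 2% mix-ups and 428 at 5%.

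**The case against.** The case against has real force. Nobody reading Section 6.1.1 in context would build a PP set that excludes every compliant patient. A reader might infer that the PP set is wrong in concept, but the reference to mix-ups and to material groups does not support that: it is a wording error.

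A reader might also infer that every patient with the same mesh on both sides dilutes the result. Section 4.4 rules this out for synthetic mesh on both sides.

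Nor does the plan ignore mix-ups. The operation case report form asks whether the patient was treated as randomised, and PP and as-treated analyses are required whenever a mix-up occurs. With no mix-up, PP and ITT coincide on this ground. The bias would therefore be visible.

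The size is also open to challenge. No mix-up rate is stated, and 23 wrong-sided implantations would be many. The 4.8% rests on an SE of 1.02, which at 8% against 5% would need a within-patient correlation of about 0.63: (0.1211 - 451 × 0.0102²)/(2√(0.0736 × 0.0475)) ≈ 0.63. All rates assume a true difference exactly at the margin, whereas Section 6.1.5 plans for 0 to +1.

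All of this stands, and it limits the size. It does not supply a rule for a case in which ITT meets the margin and PP does not. The analysis plan, which is not shown, may contain one. The Protocol itself, however, fixes ITT for all endpoints and bases the conclusion on one interval.

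**Conclusion.** The point holds in a limited form. The violation wording in Section 6.1.1 contradicts the Surgery (D1) text and Section 4.6.1 and should be corrected, although the intended meaning is recoverable. The recurrence decision rests on ITT alone, where swaps and biological mesh on both sides act in favour of non-inferiority, and PP has no stated role.

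The effect is small at plausible-looking shares (2.7-3.3% against 2.5% for 1-2% swapped) and moderate at 5% swapped (3.8-4.8%). These figures depend on assumed mix-up shares, on mix-ups unrelated to outcome, on an SE between 1.02 and 1.64 points, and on a true difference of +3 points. They do not show that a non-inferiority claim from this trial would be false. A fuller list of PP violations, and the handling of same-mesh patients in the paired as-treated tests, can be left to the analysis plan.

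**What to change.** In Section 6.1.1, replace the reference to the same procedure with the same mesh material on both sides, so that the rule no longer collides with Surgery (D1) and Section 4.6.1.

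In Section 6.1.3, state that non-inferiority for recurrence is claimed only if the upper 95% limit lies below +3% in both the ITT and the PP set. Requiring both keeps the false-claim rate at or below that of the stricter set.

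The cost is a few words, one more analysis in the decision, and a slightly harder claim. With 5% of patients removed, the PP interval is wider by a factor of √(451/428) = 1.03, so a half-width of 2.00 points becomes about 2.05. If no mix-ups occur, the two sets coincide on this ground and the requirement costs nothing.
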